## Theoretical rationale

### Self-Determination Theory and motivation for health behavior

Many recent studies have shown the crucial role that motivated behaviors, such as regular exercise, following a healthy diet, and not smoking, can play in the maintenance of health [11]; many people at health risk have the means readily at hand to improve their condition, assuming that they are willing to act. In fact, the failure of many people to adhere to healthy behaviors represents a public health problem, one with many causes but for which a considerable part is motivational in nature. This highlights the need for a clearer understanding of what motivation is and how to facilitate it in the context of health behavior. Motivation refers to the psychological forces or energies that impel a person toward a specific goal. However, for many years, motivation was viewed in a one-dimensional way, as varying only in amount or quantity. Introducing the issue of *quality *of the motivational drive, Deci and Ryan [12,13] developed the Self-Determination Theory (SDT) which distinguishes between *amotivation *(lacking any intention to engage in a behavior), *extrinsic motivation *(where the behavior is engaged in order to achieve outcomes that are separable from the behavior itself) and *intrinsic motivation *(where the behavior is engaged in for the enjoyment and satisfaction inherent in taking part). In addition, SDT distinguishes between qualitatively different forms of extrinsic motivation, by contrasting *autonomous *or *self-determined *vs. *controlled *or *non-self-determined *types of behavioral regulation. This distinction is represented as a continuum and is characterized in terms of the degree to which the regulation of a behavior has been internalized so that it is engaged in with a true sense of volition and choice. Motivation is autonomous to the extent that a person's perceived locus of causality is *internal *(i.e. the perceived source of initiation and regulation for motivated behaviors emanates from the self). Motivation is controlled to the extent that people act because they feel pressured or compelled to do so, either by others or by themselves, and this involves having an *external *perceived locus of causality [14].

According to Deci and Ryan, intrinsic motivation is linked to greater productivity, creativity, spontaneity, cognitive flexibility, and perseverance [12]. However, most human behaviors are not intrinsically motivated, which highlights the importance of studying extrinsic forms of motivation. Four types of extrinsic motivation have been described, which can be located on a self-determination continuum [15]. *External regulation *is at the lower end of the continuum. It means doing something in order to gain a reward or to avoid a punishment administered by others. *Introjected regulation *involves an internal feeling of obligation, a need to act in order to avoid feelings of guilt (although the pressure stems from inside, the individual does not feel free regarding the behavior). *Identified Regulation *concerns doing something based on the value of its consequences. In this case, the individual feels free to act and does so because the outcomes are personally important. Finally, when a behavior is coherent with the person's other values, personality schemas and sense of self, the regulation is fully self-determined and said to be *integrated*. SDT proposes that human motivation, vitality, development, and psychological adaptation can be explained by the process of *internalization*, that is, movement along this continuum [13]. A model describing internalization and human motivation is presented in Figure 1.

**Figure 1 F1:**
[figure not shown]
**Model Describing Internalization and Human Motivation**. Model shows different types of motivation and regulation *continuum *reflecting varying degrees of internalization and self-determination. This *continuum *reflects *a simplex-ordered *structure, evident when the correlation between scales measuring adjacent types of motivation such as *external *regulation and *introjected *regulation is higher than the correlation between dimensions that lie further apart such as *external *regulation and *identified *regulation. Adapted from [68].

Autonomous behavior is an expression of one's self and is undertaken with a full sense of choice, accompanied by an internal perceived locus of causality and a sense of true volition. Importantly, according to this theory, autonomously motivated behaviors are more likely to result in meaningful, long-lasting changes. Conversely, behaviors that are controlled by rewards and punishments or by self-imposed pressures are predicted to last only as long as the contingencies or pressures remain in place.

Fortunately, according to SDT, formerly controlled motivation can be internalized and transformed into autonomous motivation, if supportive conditions are in place. In fact, this contemporary theory of human motivation focuses on the psychological nutriments that engender adaptive motivational, behavioral, cognitive, and affective outcomes, by specifying contextual variables that facilitate (or hinder) these processes. The way a person acts in a particular setting cannot be attributed only to individual differences; contextual variables also exert a significant influence. Thus, SDT also considers the influence of the social environment on motivation. According to Deci and Ryan [13], although people have an inherent propensity toward maintaining their well-being, this natural tendency can be thwarted by conditions that frustrate the satisfaction of three basic psychological needs. These needs are for *autonomy *(feeling volitional and feeling choice and responsibility for one's behavior), *competence *(feeling that one can accomplish the behaviors and reach the goal) and *relatedness to others *(feeling understood, cared for and valued by significant others). In the context of health, socio-environmental conditions that facilitate the satisfaction of these needs will promote the internalization of protective and preventive health behaviors so that they are engaged in autonomously and more likely to be maintained in the long term. A recent study in the context of exercise adherence clearly indicated that fulfillment of these three basic needs was related to more self-determined motivational regulations [16]. It can generally be stated that people need to feel a sense of choice and volition with respect to their health-related goals; they need to understand how to attain these goals and feel that they can be effective in carrying out the necessary actions; and feel respected and cared for by practitioners and important others. This means that people not only need to feel that they can carry out a certain behavior (confidence, efficacy, competence), they also need to feel that they are fully responsible for initiating and maintaining that behavior and that they are doing so willingly (autonomy, self-determination, responsibility).

According to SDT, a person will develop and maintain more self-determined motivation when the personal context around them is *autonomy supportive*. The idea of autonomy support refers to eliciting and acknowledging peoples' perspectives, supporting their initiatives, offering choice/options, and providing relevant information, while minimizing pressure and control. Previous research has demonstrated that when physicians are perceived by their patients as being autonomy supportive, patients report greater self-motivation for treatment adherence [17]. Another recent study, designed to test a SDT intervention for motivating tobacco cessation in a clinical trial [18], showed that intervention participants perceived greater autonomy support and reported greater autonomous and competence motivations than did controls, supporting the causal role of autonomy support in the internalization of more internal forms of regulation.

### Self-Determination Theory, exercise and weight control

According to SDT's basic tenets, successful maintenance of weight reduction would occur when people chose eating and exercise behaviors because they personally value weight loss maintenance and its health benefits. Lasting behavior change necessary for maintenance depends not on complying with demands for change but rather on accepting the regulation for change as one's own. In other words, it requires internalizing values and regulation of relevant behaviors and then integrating them with one's sense of self so they become the basis for autonomous regulation. Accordingly, successful weight loss and long-term maintenance would not be achieved if reasons for it were mostly controlling (e.g., because the doctor insisted or based on a strong desire to be thin, according to social norms). Being autonomous in one's relevant actions, that is, having an internal perceived locus of causality, is the crucial predictor of maintained behavior change [19]. In a study specifically designed to study the effects of motivational factors during a weight control program, results showed that the degree of autonomous motivation predicted not only attendance at weekly meetings and weight loss during the program, but, more importantly, maintenance of weight loss at the 23-month follow up [20].

The role of exercise in weight management has also been analyzed in relation to SDT. In a recent study on psychosocial predictors of weight management, increase in intrinsic motivation for physical activity was the strongest predictor of long-term weight change, even after adjusting for initial weight-loss [21]. The authors stressed the importance of ensuring that individuals take on physical activities that they intrinsically enjoy, feel competent at, and that contribute positively to their sense of autonomy as key factors for greater success in the difficult task of long-lasting weight control.

A common theme emerging from the problem of exercise adherence concerns the role of individual's reasons for exercising (participation motives) in determining long-term adherence to regular physical activity. Markland's study findings [22] support the idea that extrinsic motives such as exercising for weight control or because of a doctor's exercise prescription may be perceived as controlling thereby undermining self-determination and leading to a lack of enjoyment of exercise. On the contrary, intrinsic motives, such as exercising for enjoyment may be perceived as informational, enhancing perceptions of self-determination, suggesting that controlling exercise regulations may lead to a greater number of relapses from exercise compared with more self-determined types of exercise regulation. Importantly, exercisers in the maintenance stage of change display significantly more self-determined motivation to exercise than those in the preparation and action stages [23]. Also, others have shown that adherence to exercise in individuals participating in fitness classes is higher when intrinsic motives related to enjoyment and feelings of competence were reported, compared to when body related outcomes (conceptualized as extrinsic) are the primary motivation [24]. Another study on perceived autonomy support for exercise concluded that participants who exercised regularly report modest to large changes in relatedness and competence need satisfaction and intrinsic motivation over time, providing theoretically-sound insights into reasons why people persist with exercise behaviors [25].

The mechanisms that promote self-determined motivation for exercise are now under investigation. Overall enjoyment, perceptions of competence, and intrinsic reasons for participation appear to play a central role in the maintenance of physical activity behaviors [23]. In a large scale RCT, increases in enjoyment mediated physical activity in female adolescents involved in a school-based intervention [26]. In fact, while longitudinal studies are required to better understand the processes underlying maintained exercise behavior, previous results support Markland and Hardy's [27] proposition that an individual's motivational focus needs to shift from extrinsic to intrinsic for long lasting results. New models are needed to understand this shift. We argue that understanding the motivational basis of long-term weight management and exercise requires adopting a more general model of motivation than that offered by the behaviorist tradition, which focuses on controlling a person's behavior with rewards and punishments and on the external determinants of behaviors. It also requires adopting a model more general than that offered by the social cognitive tradition, characterized by a higher emphasis on expected outcomes and enhancing patients' sense of confidence or self-efficacy (quantity of motivation) but not focusing on the quality of motivation, sense of autonomy, and locus of causality [28]. Self-Determination Theory provides such a model.

### The Self-Determination Theory model for maintained behavior change

Figure 2 presents the self-determination model of health behavior change and the expected relationships among its key constructs. Central to the model is autonomous self-regulation for behavior change. Autonomy support, both experimentally manipulated and as perceived by patients, and also a participant's general autonomy orientation are predicted to enhance autonomous self-regulation and perceived competence. Autonomous self-regulation and perceived competence are in turn expected to increase maintained change of the health-risk behaviors [29].

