Primarily, we will evaluate the extent to which a more internal self-regulatory style, higher intrinsic motivation, and more internal perceived locus of causality (regarding exercise behavior) act as mediators of sustained exercise adherence and weight loss. Motives to exercise are also expected to mediate the impact of the intervention on behavioral outcomes; psychological, interpersonal, and health-related motives are hypothesized to positively predict long-term exercise participation. Secondly, individual differences in general causality orientations and perceived treatment climate will be evaluated as moderators of intervention effects; more successful participants are expected to show a more autonomous (less controlling) general orientation style and to describe the treatment interpersonal environment as more autonomy-supportive. A comparison group is included in the research design, to adequately test intervention-specific moderation and mediation hypotheses [10].

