### Statistical analyses

Analysis will be conducted for completers-only and using an intent-to-treat model. Baseline data imputation for missing scores at follow-up will be employed by default. Despite limitations of any imputation strategy, this method is conservative and has been recommended before [63]. The use of these models is very important in clinical trials where completion is less than perfect, since completers-only analyses can be severely biased and underpowered [44].

For analysis of moderators and mediators, we will follow recommendations by Kraemer et al. [10]. Generally, for each primary outcome, linear models with be conducted to test for 1) main effect of intervention (I), 2) main effects of each moderator or mediator (M), 3) interactive effects of M and I, 4) overall effect of intervention (plus high vs. low M) and 5) effect of intervention for sub-groups of subjects at specific levels of M. A moderator will be defined as a baseline variable (thus uncorrelated with intervention) that interacts with intervention assignment to produce significant effects. The overall effect of intervention ("additive" effect of intervention and M) will represent the actual (clinical) impact of intervention participation in the presence of M. Finally, profiles of subjects with particular values of M may be identified who are responsive to this particular SDT-based intervention.

Measures of central tendency and distribution will be examined for body weight and psychosocial variables at the different measurement periods. Repeated measures ANOVA and ANCOVA General Linear Model will be used to assess change in dependent variables and to test for within-and between-group differences. Multiple regression analyses and recursive partitioning (signal detection methodology) [64] will be employed to identify characteristics/profiles associated with success, following the principles enunciated above.

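### The listed mediator models name no baseline motivation term and do not say how the mediator is scored, so the mediator-to-outcome path is open to confounding that the article's own theory predicts

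*Protocol article*

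**What the plan says.** The Background of the Protocol article puts mediation first: a more internal regulatory style, intrinsic motivation and internal locus of causality are to be evaluated as mediators of exercise adherence and weight loss. As a second aim, "individual differences in general causality orientations and perceived treatment climate will be evaluated as moderators of intervention effects", with the expectation that "more successful participants are expected to show a more autonomous (less controlling) general orientation style".

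The section on the Self-Determination Theory model says that autonomy support and "a participant's general autonomy orientation are predicted to enhance autonomous self-regulation and perceived competence". The legend of Figure 2 says that orientation reaches maintained change by way of both competence and self-regulation. An earlier theory section describes internalisation as a process, "that is, movement along this continuum".

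Statistical analyses lists what the linear models test for each primary outcome. After the main effect of intervention come "2) main effects of each moderator or mediator (M), 3) interactive effects of M and I", then the overall effect and the effects at specific levels of M. Baseline variables have one stated role in these models: "A moderator will be defined as a baseline variable (thus uncorrelated with intervention) that interacts with intervention assignment". ANCOVA is mentioned separately, for change in dependent variables, with no covariates named. The section does not say whether M is a follow-up or a change score.

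**The concern.** A mediation claim needs two links. The link from I to M is protected by randomisation. The link from M to the outcome compares women who differ in M within an arm, and randomisation does nothing for that comparison. Any pre-randomisation characteristic that raises M and also relates to the outcome distorts it.

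The article names such a characteristic. General autonomy orientation is placed before the mediators and is expected to be higher in successful women. The models appear to take one M at a time. On the article's own diagram, orientation then also reaches the outcome through the mediator that is not in the model, so it confounds each single-mediator model even without a direct effect on the outcome.

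The baseline score of the mediator raises the same issue. A follow-up score mixes where a woman started with how far she moved, and the theory concerns the movement.

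The trial's leading mechanistic conclusion is at stake. The randomised comparison of the arms is not affected.

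**Working it through.** **Inputs from the article (Sample size and power; Recruitment).** Arm effect on psychosocial variables: 0.67 SD (the lower figure given). Benchmarks for a moderate and a strong association: 0.22 and 0.31. These reproduce from 5% and 10% of variance: √0.05 = 0.224 and √0.10 = 0.316. Entrants 258 less 20% dropout: 258 × 0.8 = 206, so √N = 14.35. Two-sided α = 0.05. The article gives no figure for the mediator models themselves.

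**Assumptions not in the article.** Correlation r of baseline with follow-up mediator: 0.3 to 0.7. Slope g of the outcome on baseline mediator, apart from follow-up mediator: 0.10, or the generic benchmark 0.22. All variables have SD 1 within arm.

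**Formulas.** Let M0 be the baseline score and let the outcome be b·M + g·M0 + noise within arm, so b is the true mediator slope. The listed model then estimates:
- M as follow-up score: b + g·r
- M as raw change: (b − g)/2
- M as follow-up score with M0 as covariate: b

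With b = 0, z = g·r·√N for the follow-up score and z = (g/2)·√(2(1 − r)N) for raw change. The rejection rate is Φ(z − 1.96) + Φ(−z − 1.96).

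**No true mediator effect (b = 0), N = 206.**

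| g | r | Follow-up slope | z | Significant |
|---|---|---|---|---|
| 0.10 | 0.3 | 0.030 | 0.43 | 7% |
| 0.10 | 0.7 | 0.070 | 1.00 | 17% |
| 0.22 | 0.3 | 0.066 | 0.95 | 16% |
| 0.22 | 0.7 | 0.154 | 2.21 | 60% |

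Simulation of the model with I, M and I × M gives 6-17% at g = 0.10 and 16-58% at g = 0.22. With all 258 women, the simulated range at 0.22 is 19-69%. The false indirect effect at g = 0.22 runs from 0.67 × 0.066 = 0.04 SD to 0.67 × 0.154 = 0.10 SD. If the intervention does not move M, both steps are passed in at most about 5% of runs.

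With raw change and g = 0.22, the slope is −0.11, the wrong sign. It is significant in 46% of trials at r = 0.3 (z = 1.87) and 23% at r = 0.7 (z = 1.22); simulation gives 22-46%.

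With M0 as covariate, the slope is about 0 and 4-6% are significant in every setting.

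**Masking.** With b = 0.22 and g = 0.22, the raw-change slope is (0.22 − 0.22)/2 = 0, so a real mediator disappears. With b = 0.22 and g = 0, it is halved to 0.11.

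**Trait alone, through a second mediator.** If orientation correlates t with each of two mediators and only the second acts on the outcome, with slope b2, the false slope on the first is t²·b2. With assumed t = 0.31 to 0.5 and b2 = 0.22 to 0.31, this is 0.021 to 0.078. The formula then gives about 6% to 20% significant; simulation put the range at about 6-17%.

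**Power cost of adjusting (b = 0.22, g = 0, r = 0.6).** Unadjusted: z = 0.22 × 14.35 = 3.16, about 88%. Adjusted: z = 3.16 × √(1 − 0.36) = 2.53, about 71%. Simulation gives 87% and 69%.

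**The case against.** A reader might infer that the plan excludes baseline adjustment and that pre-existing differences will be reported as mediation. The article supports neither. Its list is introduced as a general approach, names effects to be tested rather than full equations, defers to cited recommendations, and mentions ANCOVA with unnamed covariates. A covariate list may stand in a fuller document. False mediation also requires M to be a follow-up score and the intervention to move it. The theory's language leans towards change, and raw change errs in the other direction.

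Raw change is not always wrong. If the outcome is driven by mediator change itself (g = −b), the raw-change slope is (b + b)/2 = b. It is then unbiased and somewhat more powerful than the adjusted model (about 80% against 70% for a slope of 0.22 at r = 0.6).

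The sizes are soft. The benchmarks of 0.22 and 0.31 are generic, the stability is assumed, and the main scenario needs baseline motivation to matter apart from follow-up motivation. The article's diagram shows no direct path from orientation to the outcome. At g = 0 there is no excess error from the baseline score, and the trait alone produces a modest one.

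All of this limits the claim. It does not meet the central point: the article does state model terms, gives baseline variables only a moderator role there, and has a theory in which a baseline trait precedes both mediators. ANCOVA is attached to outcomes, not to these models. Neither scoring of M makes the listed model safe in general.

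**Conclusion.** The concern holds in a limited form. As listed, the mediator models leave the M-to-outcome path open to confounding by baseline motivation, and the unstated scoring of M decides whether the error invents mediation or hides it. For a null follow-up-score M with 206 women and r between 0.3 and 0.7, false significance is about 6-17% at a baseline slope of 0.10 and 16-58% at 0.22, against 5%. Orientation acting alone through a second mediator gives about 6-17%. All these figures depend on stabilities and slopes that the article does not supply, and they shrink to nominal as those slopes approach zero. The point bears on the interpretation of the leading mediation hypothesis; it does not show that a false result will occur.

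**What to change.** In Statistical analyses, state that each mediator model regresses the outcome on I, the follow-up score M, I × M and the baseline score of that same mediator, and also includes the baseline General Causality Orientations autonomy score. Say that M is then read as change given the starting level. In the formulas above, this slope equals b whether the outcome follows the follow-up score or the change.

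The cost is wording and about two degrees of freedom. A baseline assessment is planned, and the orientation scale is already in the battery. Some power is lost if baseline motivation has no separate effect: about 87% to 69% for a true slope of 0.22 at r = 0.6. The return to 5% in the calculations is partly by construction, because they contain only the adjusted confounders, measured without error. Measurement error and other common causes of mediator and outcome would remain, and the report should say so.
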